**Methodology::**

The proposed feasibility trial will be a single-arm, single-center study. A total of 47 ESRD patients awaiting kidney transplantation will be selected as subjects to undergo personalized family exercise pre-rehabilitation, including aerobic exercise, functional resistance exercise, and flexibility training. Briefly, a 6-minute walking test (6MWT), 4-meter gait speed, grip strength, and sit-to-stand test will be used as the main outcome indicators. The effect of family exercise pre-rehabilitation on the optimization of body function in ESRD patients undergoing kidney transplantation will be assessed. The days of hospitalization after kidney transplantation, postoperative complications, health survey (the Short Form Health Survey, SF-36), and the Hospital Anxiety and Depression Scale (HADS) will be used as secondary outcome indicators to evaluate the improvement of quality of life, psychological function, and postoperative rehabilitation of patients after kidney transplantation. These indexes will be collected before and after intervention (baseline and before kidney transplantation), before discharge (after kidney transplantation), and 1 month after discharge.

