### Setting

2.1

The study will be carried out at the Organ Transplant Center of the Second Affiliated Hospital of Hainan Medical University, a 2000-bed Grade 3A general hospital affiliated to Hainan Medical College. This hospital has obtained the national qualification for kidney transplantation in 2010, with annual kidney transplants of about 150.

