#### Secondary outcomes

2.6.2

1.Postoperative condition: the occurrence probability of postoperative complications, such as hospital stay, postoperative pulmonary infection and bleeding, postoperative drainage, and extubation time is recorded.2.Quality of life: the quality of life is evaluated by the SF-36, which includes physical function, limitation caused by the body, body pain, general health, vitality, social function, limitation caused by emotion, and mental health. The higher the comprehensive score, the better the quality of life.^[20]^3.Psychological evaluation: the HADS will be used to evaluate the emotional state of anxiety and depression. There are several problems of anxiety and depression respectively. The higher the total score, the more serious the anxiety or depression. This scale has good reliability and validity in our general hospitals.^[21]^

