### Sample size calculation

2.10

According to existing literature (Manfredini Fabio, Mallamaci Francesca, D’Arrigo Graziella et al. Exercise in Patients on Dialysis: A Multicenter, Randomized Clinical Trial.[J]. J Am Soc Nephrol, 2017, 28: 1259–1268), G-power3.1 software will be used to calculate the sample size. By paired-samples *t* test, the effect size = 0.37, α = 0.05, and power size = 0.80, and the calculated sample size is 47.

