### Statistical analysis

2.11

SPSS24.0 statistical software and Office Excel 2016 will be used to analyze the test data. The quantitative data will be tested by the Kolmogorov–Smirnov test to determine whether they are following a normal distribution. Quantitative data: if the comparison before and after the intervention follows the normal distribution, the paired sample *t* test will be used; if it does not meet the normal distribution, the non-parametric test Wilcoxon symbolic rank test will be used for analysis. The results are expressed as mean ± standard deviation (
$\bar{X}\pm S$
). The postoperative hospitalization days, postoperative complications, postoperative drainage, and extubation are compared with the previous data in the hospital. If the data satisfies normal distribution, an independent sample *t* test will be used; otherwise, the Mann–Whitney *U* test is used for analysis, and the results are all expressed as mean ± standard deviation (
$\bar{X}\pm S$
). The qualitative data will be analyzed by chi-square test (χ^2^ test), and the results are expressed as a percentage (%). The level of significance is *P* < .05.

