This Phase I trial is essential to understand potential recruitment rates, dropout rates, patients who receive transplants or die during the study, and the completion rate of this program to accurately motivate participants for future RCTs.

Collectively, this trial is a practical, single-center, single-arm, exploratory clinical trial. We plan to show that ERAS-based home exercise pre-rehabilitation will reduce the adverse effects of frailty, cardiopulmonary dysfunction, and psychological dysfunction on the prognosis of renal transplantation.

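### The tests fixed in section 2.11 for comparing participants with past hospital patients have no safeguard for rare events or unequal spread, so the 5% level may not hold (minor)

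*Protocol article*

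**What the plan says.** The Protocol article, section 2.11 (Statistical analysis), sets postoperative stay, complications, drainage and extubation against earlier patients of the same centre: these outcomes "are compared with the previous data in the hospital". Two rules follow.

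- Quantitative outcomes: "If the data satisfies normal distribution, an independent sample" t test is used; otherwise the Mann–Whitney U test. Normality is the only condition.
- Qualitative outcomes: "The qualitative data will be analyzed by chi-square test". No alternative is given for small expected counts.

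Significance is declared at P < .05. Section 2.6.2 names the outcomes concerned: "postoperative pulmonary infection and bleeding, postoperative drainage, and extubation time is recorded".

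On numbers, the abstract says "A total of 47 ESRD patients awaiting kidney transplantation will be selected as subjects". The Discussion lists as still unknown "dropout rates, patients who receive transplants or die during the study". Section 2.1 describes a centre "with annual kidney transplants of about 150". The article does not state how many past patients are used, over what period, or with what complication rates or SDs.

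**The concern.** The chi-square P value is a large-sample approximation, and the equal-variance t test assumes the same spread in both groups. The plan provides for non-normality but for neither of these.

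Both gaps could matter here. Only transplanted participants have postoperative data, so 47 is an upper limit. Pulmonary infection and bleeding may be uncommon. A centre of this volume may well supply a past group larger than the trial group. Eligibility (age 18 to 60, first deceased-donor transplant, expected wait over 12 weeks, able to exercise) could give participants a different spread from hospital records in general.

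At stake is whether one or two events, or a difference in variability alone, can decide a P value on outcomes that the Discussion stresses. Without a named alternative, the choice between competing P values is also left until the data are seen.

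**Working it through.** **The plan's own figure.** Section 2.10 gives "the effect size = 0.37, α = 0.05, and power size = 0.80" for a paired t test and obtains 47. The noncentral t distribution reproduces 47 one-sided (power 80.3%). Two-sided, 47 gives 70.0% and 60 would be needed. That is a separate matter: this calculation concerns the before–after comparison and does not size the comparison with past patients.

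**Inputs.** From the article: at most 47 participants, about 150 transplants a year, P < .05. Assumed, because not given: 30, 35 or 47 transplanted participants, 47 to 300 past patients, a common complication rate of 1% to 10%, and a ratio of trial SD to past SD of 2/3 to 1.5.

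**Chi-square: true level.** With n1 trial and n2 past patients and a common rate p, the level is the sum of Bin(a; n1, p) × Bin(b; n2, p) over all tables (a, b) with X² > 3.841.

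| Groups | 1% | 2% | 3% | 5% | 10% |
|---|---|---|---|---|---|
| 47 v 47 | 0.2% | 1.1% | 2.7% | 5.1% | 5.9% |
| 47 v 150 | 2.2% | 2.9% | 3.3% | 4.1% | 5.0% |
| 47 v 180 | 8.9% | 5.8% | 4.3% | 4.1% | 5.1% |
| 47 v 300 | 5.4% | 4.8% | 4.4% | 4.1% | 4.7% |
| 35 v 150 | 8.4% | 6.3% | 5.3% | 4.4% | 4.6% |
| 30 v 150 | 7.1% | 5.1% | 4.0% | 3.8% | 4.7% |

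**Why the excess is isolated.** With a single event, in the trial group, X² = (n2/n1) × N/(N − 1), where N = n1 + n2.

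- 35 v 150: (150/35) × 185/184 = 4.31, P = .038. Fisher's test gives 35/185 = .19.
- 47 v 180: (180/47) × 227/226 = 3.85, just above 3.841.
- 47 v 150: (150/47) × 197/196 = 3.21, P = .073.

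At a 1% rate the table 1/35 v 0/150 alone has probability 35 × 0.01 × 0.99^184 = 5.5%. For 1/47 v 0/180 it is 47 × 0.01 × 0.99^226 = 4.9%. With more past patients, zero past events becomes unlikely and the excess fades.

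**Direction.** In the rows with 150 or more past patients, at rates of 1% and 2%, essentially every false rejection says trial patients did worse. At 47 v 150 and 5%, 3.5 of the 4.1 percentage points lie on that side and 0.7 on the other (rounded). For 47 v 47 the two sides are equal.

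**t test.** Let r be trial SD over past SD, with past SD = 1. The true variance of the difference is V = r²/n1 + 1/n2. The equal-variance test uses on average E = {[(n1 − 1)r² + (n2 − 1)]/(n1 + n2 − 2)} × (1/n1 + 1/n2). The level is about 2[1 − Φ(1.972 × √(E/V))]. For 47 v 150:

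- r = 1.5: V = 0.0545, E = (252.5/195) × 0.02794 = 0.0362, √(E/V) = 0.815, level about 10.8% (simulation: about 11%).
- r = 2/3: V = 0.0161, E = (169.4/195) × 0.02794 = 0.0243, √(E/V) = 1.227, level about 1.6% (simulation: about 1.6%).

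In simulation with normal data the test keeps 4.9% to 5.1% when SDs are equal, whatever the group sizes, and 4.9% to 5.2% when group sizes are equal, whatever the SDs. Welch stays at 4.6% to 5.2% throughout. Mann–Whitney does not rescue the rule: with unequal spread at 47 v 150 and 47 v 300 its level is 2.1% to 9.7%.

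**The case against.** The strongest reply is that the trouble is conditional and often absent. A reader might infer that chi-square breaks down whenever an expected count is below 5, that is, at overall rates below 5/47 = 10.6%. The table does not support that: at 47 v 150 the level never exceeds 5% by any material amount between 1% and 10%, and much of the range lies at 4% to 5%. The single-event result also sits on a boundary, since 1/47 v 0/150 is not significant. This stands, and the excess is limited to particular group sizes with events near 1% to 2%.

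A reader might also infer that unequal groups alone invalidate the t test, or that the plan prescribes the equal-variance form. Neither holds. SDs must differ as well, and section 2.11 says only independent-sample t test. Nor does the article establish that complications are rare or the past group large; the annual volume is not the comparator size.

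Fisher's test is no full cure. It caps the error but is conservative: at 47 v 47 and a 5% rate its level is 0.6% against 5.1% for chi-square, and at 47 v 150 it is 2.7% against 4.1%. This stands too, and it bears on which exact test to name.

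Finally, an article may leave test variants to a fuller plan. That has some force, but section 2.11 is not silent. It states which test applies and on what condition, and the condition is incomplete.

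**Conclusion.** The point holds as a conditional, minor one. The rule in section 2.11 may miss its 5% level, by an amount that depends on comparator size, event rates and SDs that the article does not give. For complications near 1% to 2%, the chi-square level ranges from about 0.2% to 8–9% across the group sizes examined, and with a much larger past group the errors fall almost entirely against the intervention. At 3% to 10% it is mostly 3% to 6%. If the equal-variance t test is used and sizes and SDs both differ, 47 v 150 gives about 1.6% to 11% for SD ratios of 2/3 to 1.5.

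The t test figures assume normal data; skewed outcomes were not examined. The severity is low because these are secondary outcomes of a single-arm exploratory study and the primary before–after tests are unaffected. It would be too much to infer that correct tests make this comparison sound: past patients were not randomised, and a P value at its nominal level does not remove that bias.

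**What to change.** In section 2.11:

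- Use the Welch (unequal-variance) t test for all two-group comparisons of quantitative outcomes with hospital data, and report the mean difference with its confidence interval.
- When any expected count is below 5, use an exact test for the complication concerned, preferably unconditional or mid-P and otherwise Fisher's, and report the difference in proportions with an exact confidence interval.

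Mid-P (Fisher's P value less half the probability of the observed table) gives, by the same enumeration, 2.9% at 35 v 150 and 2.0% at 47 v 180 for a 1% rate, and 4.4% at 47 v 150 for a 5% rate. It does not strictly guarantee 5%; Fisher's test does, at the price of lower power.

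The cost is about two sentences and no extra data. Welch and Fisher are standard output in the named software; whether it offers an unconditional or mid-P test should be checked before one is named.

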### Adverse events and analysis

2.12

An adverse events (AEs) will be reported at initial screening and continue until 30 days post each participant's kidney transplantation. The symptom degree, occurrence time, duration, and treatment of AE should be recorded in the observation table, and the correlation between AEs and clinical intervention training should be evaluated based on comprehensive consideration and recorded in detail by managers. The researchers can suspend the intervention, adjust the training cycle, deal with it according to the situation, and report it to the ethics committee of the research institution and the research unit if necessary to closely observe the outcomes of the event.

## Discussion

3

With the increasing number of renal transplant operations, the continuous maturity of surgical methods, and the pursuit of better clinical outcomes, people's interest in the ERAS program has greatly increased. Pre-rehabilitation before operation can improve the baseline function of patients, enhance surgical tolerance, and reduce postoperative complications.

When waiting for renal transplantation, ESRD patients often show frailty and decreased cardiopulmonary function, leading to increased complications and mortality after renal transplantation. Preoperative pre-rehabilitation can optimize the health status of individuals before the operation. Therefore, patients can achieve better results after operation. The family based pre-rehabilitation exercise program has been proved to be effective in heart surgery, liver transplantation, and other related fields. The family sports plan is simple, and the subjects are easy to grasp the essentials of their movements, including walking, strength training, and other sports, which do not need professional equipment and are not affected by the venue, weather, and other factors. Pre-rehabilitation exercise programs for renal transplantation in the family can reduce the time and economic burden brought by dialysis patients going to the rehabilitation clinic regularly. In the present trial, we, for the first time, will assess an ERAS-based home exercise pre-rehabilitation in patients listed for kidney transplantation.

In the present study, participants will record their activities in their sports diaries and report them in WeChat groups. In a larger RCT, real-time data collection can be considered. Physiotherapists can monitor the compliance and progress of the exercise program every day and avoid reporting bias by participants.

Both objective and subjective parameters will be included in the primary and secondary outcomes. We should not only pay attention to the objective incidence of hospital stay and postoperative complications but also consider the impact on the patient-based HRQoL. Patients can return to family and society in the best state by improving HRQoL, embodying the core of diagnosis and treatment in the concept of ERAS, which is centered on serving patients.

This Phase I trial is essential to understand potential recruitment rates, dropout rates, patients who receive transplants or die during the study, and the completion rate of this program to accurately motivate participants for future RCTs.

Collectively, this trial is a practical, single-center, single-arm, exploratory clinical trial. We plan to show that ERAS-based home exercise pre-rehabilitation will reduce the adverse effects of frailty, cardiopulmonary dysfunction, and psychological dysfunction on the prognosis of renal transplantation.

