### Data collection

2.7

In addition to the data collection involving our primary and secondary outcomes, the information regarding patient demographics and clinical variables, such as age, sex, type of occupation, marital status, education, BMI, dialysis of history, and frequency, causes of ESRD, and type of renal replacement therapy, will be also collected. The above-mentioned features are selectively collected on the admission day (baseline), on the day before operation (second follow-up), on the discharge day (third follow-up), and 4 weeks post-operation (fourth follow-up). The proportion of patients who agree to participate in the trial and the reasons for disagreement will be summarized. Moreover, the number and percentage of participants who complete the complete exercise plan will be also recorded. Scheduled data collection at each time point is presented in Table 4.

**Table 4 T4:** Scheduled events and timeline of the trial.

	Study period					
	Time point	Enrollment	Preoperative	perioperative		Follow up
		12+ weeks before surgery	Before surgery or day of surgery	Discharge	1 month	
Enrollment	**Eligibility screening**	×				
	Informed consent	×				
Interventions	ERAS-based home exercise pre-rehabilitation		×			
Assessments	6MWT	×		×	×	×
	Grip strength	×		×	×	×
	4-meter gait speed	×		×	×	×
	5R-STS	×		×	×	×
	Postoperative condition				×	
	SF-36	×		×		×
	HADS	×		×		×

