### Compliance management

2.8

Given a home-based setup, it is important to promote adherence and conduct compliance management. To promote adherence to the program, a self-reported sports diary and a sports bracelet will be given to each participant to provide daily visual feedback and empower responsibility for their daily and weekly goals. Additionally, following a demonstration of the functional resistance exercises at their initial assessment, participants are provided with written and pictorial instructions, as well as a video of all of the exercises. All subjects are pulled into a WeChat group, each exercise record is uploaded to the group, and the “social comparison theory” is adopted to promote patients to complete the exercise.^[22]^ In addition to encouraging patients to complete exercise and punch on time at WeChat Group, the experimenter will conduct weekly telephone surveys to encourage patients to complete family exercise diaries. Any problem can be reported, such as pain or discomfort, to adjust the exercise prescription appropriately. The patients are encouraged during telephone counseling, and their efforts are praised.

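### The completion rate meant to inform a future RCT is liable to be overstated, because the only exercise record described is a self-reported diary shared in a peer-comparison group

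*Protocol article*

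**What the plan says.** **Completion is a result the trial is meant to deliver.** Section 2.7 commits to it: "the number and percentage of participants who complete the complete exercise plan will be also recorded". The Discussion lists, among the things the trial is needed to learn, "the completion rate of this program to accurately motivate participants for future RCTs". Section 2.7 does not name the data source for the percentage.

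**How exercise is recorded.** Section 2.8 provides that "a self-reported sports diary and a sports bracelet will be given to each participant to provide daily visual feedback", and to strengthen responsibility for daily and weekly goals. The same section says "each exercise record is uploaded to the group, and the “social comparison theory” is adopted to promote patients to complete the exercise". The Discussion confirms that what goes to the group is the diary: "participants will record their activities in their sports diaries and report them in WeChat groups".

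**Staff contact.** Section 2.8 adds that "the experimenter will conduct weekly telephone surveys to encourage patients to complete family exercise diaries". Patients can report problems on these calls and are praised for their efforts. The calls are not described as a check on the diary.

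**Better measurement is left for later.** The Discussion says that real-time collection can be considered in a larger RCT, where physiotherapists could follow compliance daily and "avoid reporting bias by participants".

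**The bracelet.** It is given to everyone (sections 2.5 and 2.8). The article does not say what it stores or that its data are collected, and Table 4 has no row for adherence or bracelet data.

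**The concern.** A diary shown to fellow patients, in a group set up so that members compare themselves, is not a neutral measuring instrument. Social comparison may raise the exercise done, the exercise reported, or both. If the diary is the only session record, the trial cannot separate these.

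The order of steps is also awkward. The authors recognise reporting bias and place the remedy in the next trial, yet the feasibility study exists to supply the figure on which that trial is planned. An optimistic completion rate would feed into the RCT's assumptions about adherence and achievable effect. It would also make a weak change in walking distance or strength harder to interpret, because ineffective exercise and exercise not done would be harder to tell apart.

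Meanwhile a device that may be able to check the walking component is already in each participant's hands.

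**Working it through.** **What can be reproduced.** The article states no completion rate, target or misreporting rate, so there is no planned figure to reproduce. The one planned number used here is the sample size of 47 (section 2.10), and it serves only to show the scale of sampling error.

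**Model.** Let *t* be the true completion rate, *s* the proportion of true completers whose records show completion, and *f* the proportion of non-completers whose records wrongly show completion. Then

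observed rate = *t* × *s* + (1 − *t*) × *f*

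and the bias is (1 − *t*) × *f* − *t* × (1 − *s*). The first term is over-reporting and the second is under-logging. The sign depends on which is larger.

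**Inputs.** All three are assumptions: *t* = 0.60; *f* = 0.10, 0.20, 0.30; *s* = 1.0 (nothing unlogged) or 0.8 (20% of completers fail to log).

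| *f* | *s* = 1.0 | *s* = 0.8 |
|---|---|---|
| 0.10 | 0.60 + 0.40 × 0.10 = 0.64 | 0.48 + 0.04 = 0.52 |
| 0.20 | 0.60 + 0.40 × 0.20 = 0.68 | 0.48 + 0.08 = 0.56 |
| 0.30 | 0.60 + 0.40 × 0.30 = 0.72 | 0.48 + 0.12 = 0.60 |

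With no under-logging, the bias is +4 to +12 percentage points. With 20% under-logging, it is −8 to 0 points. It is zero when *f* = *t*(1 − *s*)/(1 − *t*) = 0.60 × 0.20/0.40 = 0.30.

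**Other true rates, same range of *f*.**

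| *t* | *s* = 1.0 | *s* = 0.8 |
|---|---|---|
| 0.50 | 0.55 to 0.65 | 0.45 to 0.55 |
| 0.70 | 0.73 to 0.79 | 0.59 to 0.65 |
| 0.80 | 0.82 to 0.86 | 0.66 to 0.70 |

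**Scale.** For 28 of 47 completing (60%), the exact 95% confidence interval is 44% to 74%, a half-width of about 15 points. A bias of up to 12 points would be somewhat smaller than that sampling uncertainty, but the interval does not include it and a larger sample would not remove it.

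**How far the bracelet reaches.** The programme has three components: walking, resistance and flexibility training (section 2.5). Walking is prescribed in countable form, five times a week with 30 minutes of exercise in each session (Table 1), so a stored activity record could be compared with it. The article does not say that the device registers resistance or flexibility work. It should not be counted on for those components.

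**The case against.** Several points on the other side are fair.

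- **The source of the completion percentage is not stated.** A reader might infer that section 2.7 takes it from diaries, or that the bracelet serves feedback and nothing else. Neither is written. This is a condensed article, and a fuller protocol may cover device downloads. What stands is narrower: the article does state how activity is recorded, by diary reported to the group, and it defers better collection to a later trial.
- **Certain upward bias is not supported.** A reader might infer that the rate will be too high. Over-reporting is the likelier direction, but under-logging works against it, and the table above includes combinations with zero or negative bias.
- **Social comparison is an adherence technique.** Section 2.8 uses it to promote completing the exercise. It would be wrong to say that the plan uses it to make patients report exercise. The risk to reporting is a side effect of making the record visible to peers.
- **Other information exists.** Section 2.5 has illness-related interruptions entered in the case report table, and staff telephone weekly. These help, but neither is described as verifying sessions done.
- **The primary outcomes are performance tests.** They do not depend on the diary, so it would go too far to say that a null functional result could not be told apart from non-adherence. It would only be harder to interpret.
- **Completion is not a listed primary or secondary outcome, and the authors acknowledge reporting bias.** Both are true. Completion is still one of the Discussion's stated reasons for the trial, and acknowledging the bias does not reduce it in the figure passed on.

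**Conclusion.** The point holds as a risk to a stated feasibility result. The only session record described is self-report to a peer-comparison group, and the completion rate drawn from this trial is therefore liable to be overstated. Its size cannot be derived from the documents. Assuming 60% true completion and false claims by 10% to 30% of non-completers, the observed rate would be 64% to 72% with no under-logging, or 52% to 60% if 20% of completers fail to log. Uncertainty about the direction of the error strengthens the case for a second source. The plan should be changed, but the point does not invalidate the trial or its primary outcomes.

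**What to change.** In sections 2.7 and 2.8:

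1. Name the data source from which completion is judged.
2. Where the issued bracelet stores activity, collect it, for example at the weekly call, and make it the main measure of walking adherence against the prescribed five sessions a week.
3. Keep the diary as the record for resistance and flexibility sessions and as the second record for walking.
4. Report the agreement between bracelet and diary for walking.
5. State that completion of the resistance and flexibility components remains self-reported, so that an overall completion figure is not presented as objectively verified.

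The cost is modest: the devices are already issued and weekly contact is already planned, so the addition is some data handling. The drawbacks are that the measure depends on what the device stores and on participants wearing it, and that it can check only one of the three components.
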